## Abstract

**Background:**

The ideal rehabilitation strategy following lumbar spinal fusion surgery has not yet been established. This paper is a study protocol, describing the rationale behind and the details of a cognitive-behavioural rehabilitation intervention for lumbar spinal fusion patients based on the best available evidence. Predictors of poor outcome following spine surgery have been identified to provide targets for the intervention, and the components of the intervention were structured in accordance with the cognitive-behavioural model. The study aims to compare the clinical and economical effectiveness of a cognitive-behavioural rehabilitation strategy to that of usual care for patients undergoing lumbar spinal fusion surgery.

**Methods/Design:**

The study is a randomized clinical trial including 96 patients scheduled for lumbar spinal fusion surgery due to degenerative disease or spondylolisthesis. Patients were recruited in the period October 2011 to July 2013, and the follow-up period is one year from date of surgery. Patients are allocated on a 1:2 ratio (control: intervention) to either treatment as usual (control group), which implies surgery and the standard postoperative rehabilitation, or in addition to this, a patient education focusing on pain behaviour and pain coping (intervention group). It takes place in a hospital setting, and consists of six group-based sessions, managed by a multidisciplinary team of health professionals.

The primary outcomes are disability (Oswestry Disability Index) and sick leave, while secondary outcomes include coping (Coping Strategies Questionnaire), fear-avoidance belief (Fear Avoidance Belief Questionnaire), pain (Low Back Pain Rating Scale, pain index), mobility during hospitalization (Cumulated Ambulation Score), generic health-related quality of life (EQ-5D) and resource use. Outcomes are measured using self report questionnaires, medical records and national registers.

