## Background

For sufferers of chronic and severe back pain, lumbar spinal fusion (LSF) surgery is a commonly offered treatment strategy when conservative treatment has failed [1,2]. In the past two decades reports have indicated significant increases in spinal fusion rates in the western countries, with the largest increase seen in the US. Here the annual age and sex adjusted rates of LSF procedures increased with 220% in the period 1990 – 2000 [3] and another 170% in the period 1998–2008 [4]. These rises are in part due to advances in surgical fusion techniques and devices, e.g. the approval of intervertebral fusion cages in 1996, intended to improve postoperative outcomes [5,6]. The increasing number of LSF operations and the consequent increased costs and risk of complications and adverse events [6-9] may be justified by the benefits of the procedure. But the efficacy of LSF for degenerative spinal disorders has not yet been established, as published reviews on the subject disagree [10-12]. One review including randomized, nonrandomized and retrospective studies concluded that the body of literature supports LSF as a viable treatment option for chronic LBP [11]. Two other reviews included only randomized controlled studies (RCT) comparing LSF to conservative treatment [10,12]. The earliest review concluded that robust conclusions on the efficacy of LSF could not be made. In the latter publication the authors stated that there is strong evidence that LSF is no more effective than conservative treatment. In both reviews the comparable effect of the conservative treatment was in evidence only with the use of structured rehabilitation with a cognitive-behavioural approach (CBT). Whether an additive effect can be achieved by combining LSF with a postoperative rehabilitation strategy applying CBT has been investigated in only one study [13]. Here, LSF followed by a 12 week intervention combining CBT and a structured exercise program resulted in significantly better outcomes on disability, pain and return to work compared to LSF plus standard rehabilitation. The standard rehabilitation consisted of a 12 week home based exercise program, commencing with one instruction from the physical therapist at the hospital at discharge. Another RCT including behavioural elements in the rehabilitation intervention following LSF similarly found benefits of the intervention, compared to both 8 weeks supervised exercise and to a video-guided home-based exercise program similar to that of Abbott et al. [14].

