## Methods/Design

### Trial design

The study is a randomized clinical trial with 1-year follow-up.

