### Participants

Patients eligible for inclusion were persons at the age of 18–64 years scheduled for lumbar spinal fusion surgery (maximum of 3 adjacent vertebrae) due to pain and disability as a consequence of degenerative diseases or spondylolisthesis grade 1 or 2. Patients were included from two hospitals in the same uptake area covering 1,272,510 inhabitants.

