### Interventions

#### **
*Control group*
**

Patients in the control group received usual care, being the department's standard care related to their surgical procedure. In one of the hospitals usual care included a voluntary information meeting for patients and their spouses/relatives, approximately 2 weeks prior to surgery. Patients were routinely called for a control visit with the operating surgeon at 3 and 12 months. Following the 3 months control visit, patients commenced physical rehabilitation in their local community (e.g. physical therapy clinic or rehabilitation centre). This typically consists of 1–2 individual sessions followed by 10 sessions of supervised group-based exercise.

#### **
*Intervention group*
**

In addition to the described usual care (surgery and physical rehabilitation), patients in the intervention group participated in a patient education using a cognitive-behavioural therapy (CBT) approach.

##### 

**Structure** The CBT intervention consisted of six sessions, each of three hours duration. Patients were to attend four of the sessions prior to surgery, while the fifth and sixth sessions were placed postoperatively, at three and six months respectively. The length of the intervention was designed to optimize attendance with the time required to develop the needed skills. A previous study found no difference in outcome between programs of 15, 30 or 60 hours duration [38]. A group format was used for the intervention, as evidence suggests that there is no difference in outcome between individual and group therapy [39].

##### 

**Setting** The six sessions of the patient education took place in a conference room at the hospital, where most of the patients were to undergo surgery. The room was placed in an administrative building and hence did not have the look of a typical hospital ward. The room was big enough for the participants to move around, sit or stand as they pleased.

##### 

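### Follow-up is counted from surgery, an event after randomisation, so patients not operated have no defined one-year endpoint and sick leave before surgery is outside the window

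*Protocol article*

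**What the plan says.** All references are to the protocol article.

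- **Origin of follow-up.** The abstract (Methods/Design) states that "the follow-up period is one year from date of surgery". The Trial design section gives a length but no origin: "The study is a randomized clinical trial with 1-year follow-up". No other origin appears.
- **Who is randomised.** The abstract describes a "randomized clinical trial including 96 patients scheduled for lumbar spinal fusion surgery". The Participants section likewise admits "persons at the age of 18–64 years scheduled for lumbar spinal fusion surgery". Patients therefore enter before the operation.
- **When the intervention is given.** Under Interventions (Structure): "The CBT intervention consisted of six sessions, each of three hours duration". Then: "Patients were to attend four of the sessions prior to surgery". The other two come after the operation, since "the fifth and sixth sessions were placed postoperatively, at three and six months respectively".
- **Outcomes affected by the origin.** Sick leave/return to work is a primary outcome alongside the ODI (Outcomes), with sick-leave compensation taken from the DREAM register. The economic section plans a cost per QALY and a cost for each day by which return to work is brought forward, from health care, patient and societal perspectives.

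**The concern.** In a randomised comparison the clock should start at an event that allocation cannot affect. Surgery is not such an event here. It comes after allocation and, for the intervention arm, after most of the programme. Whether and when a patient is operated on could plausibly depend on the arm. The article's Background gives one reason: in two reviews of randomised trials, conservative care compared well with fusion only when it was structured rehabilitation on cognitive-behavioural lines. Fitting in four sessions could also alter the wait.

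Two consequences follow from the rule as written:

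1. A randomised patient whose operation is cancelled has no start date, so no date at which a one-year outcome is due. If such patients are not followed, the groups compared are no longer the groups randomised.
2. Outcomes that accumulate over time are cut off at the front. Preoperative Session D (Table 1) covers the rules and procedures for sick leave and return to work, so the intervention addresses a primary outcome during a period that the window leaves out. A longer wait in one arm would also go uncounted.

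**Working it through.** **The plan's own sample size.** Inputs from Sample size and data analysis: SD 14, difference 10, significance level 0.05 (two-sided assumed, since it reproduces the figure and one-sided gives 57), power 0.80, ratio 2:1.

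- Control n = (1 + 1/2) × [14 × (1.960 + 0.842) / 10]² = 23.1, rounded up to 24.
- Total = 24 + 48 = 72. With 10% loss: 72 / 0.9 = 80. Both stated figures are reproduced.
- The origin of follow-up does not enter this formula, so moving it leaves 72 and 80 unchanged.

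**Share of the intervention before time zero.** Inputs from Interventions (Structure).

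- Sessions: 4 / 6 = 67%.
- Hours: (4 × 3) / (6 × 3) = 12 / 18 = 67%.

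This share shows that randomisation must precede surgery, which the article does not state directly. It is not in itself a measure of harm.

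**What the rule leaves out.** Let R be randomisation and S surgery. The window is S to S + 1 year.

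- Not operated: S does not exist, so the window is undefined.
- Operated: the interval R to S is excluded. If one arm waits d weeks longer on average, and a fraction p of that time is spent on sick leave, a difference of d × p weeks is missed. The article gives neither d nor p.

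**Precision if patients cannot be evaluated.** Normal-approximation power for the ODI with 96 randomised:

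| Share not evaluable (assumed) | Power |
|---|---|
| 5% | 0.895 |
| 10% | 0.879 |
| 20% | 0.839 |

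If cancellations came on top of the planned 10% loss, keeping 72 evaluable would need 72 / (0.9 × 0.98) = 82, 72 / (0.9 × 0.95) = 85 or 72 / (0.9 × 0.90) = 89 patients, for assumed cancellation rates of 2%, 5% and 10%. All are below 96. The issue is bias and definition, not power.

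**Illustration of bias in the ODI.** All inputs here except the arm sizes are assumptions. At 2:1, 96 patients split 64 and 32. Suppose 6 of 64 intervention patients are not operated, their ODI differs from the rest by 15 points, and they are left out.

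- Shift in the intervention mean: 6/64 × 15 = 1.4 points, 14% of the 10-point target and 0.1 SD.
- If 3 of 32 controls are also not operated and differ by the same amount: 3/32 × 15 = 1.4 points, and the net bias is 1.4 − 1.4 = 0.

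The between-arm bias can therefore range from nothing upwards, depending on quantities that the article does not give.

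**The case against.** The opposing case is substantial, and much of it stands.

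- **Anchoring visits to surgery suits the question.** The aim concerns patients having fusion, and the hoped-for benefit is earlier return to work after it. Timing the ODI from randomisation would mix patients at different stages of surgical recovery. This stands: the ODI schedule for operated patients should not change.
- **Delivery before the window is intended.** A reader might infer that giving two thirds of the programme before time zero is itself a flaw. It is not. For an ODI taken at a fixed visit, treatment is meant to precede the outcome.
- **Session costs need not be lost.** A reader might infer that the cost comparison omits the preoperative sessions. The economic section micro-costs the intervention without limiting this to postoperative sessions, and it values patients' costs and time. What remains exposed is sick leave, other resource use and QALYs before surgery.
- **No exclusion is stated.** A reader might infer that patients not operated drop out of every outcome, or that the randomised comparison is already broken. The article does not say so. It gives no analysis restricted to operated patients and no start date for the DREAM extract, and a fuller protocol may cover both.
- **The mechanism is conjectural.** The reviews concern conservative care instead of fusion. Here the education is added to planned surgery, and three of the four preoperative sessions include preparation for it. Nothing shows that it changes who is operated on.

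The objection does not remove the rule. The article states one origin, and that origin is a post-randomisation event. This is a fault in something stated, not a complaint about missing detail.

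**Conclusion.** The point holds in limited form. As written, the rule starts follow-up at an event after randomisation that the intervention could influence. It defines no one-year endpoint for a randomised patient who is not operated, and it leaves the time between randomisation and surgery out of sick leave, other resource use and QALYs.

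The size of any bias cannot be given, because the article reports neither a cancellation rate nor a waiting time. The 1.4-point figure is an illustration and vanishes if cancellations are alike in both arms. The conclusion rests on randomisation preceding surgery, which follows from the four preoperative sessions, and on the abstract's rule being applied literally. It should be settled before analysis, mainly because sick leave is a primary outcome that accumulates over time.

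**What to change.** 1. Keep the surgery-anchored ODI visits for operated patients.
2. For patients not operated, time the 12-month ODI from the originally planned surgery date, and analyse them in their allocated group.
3. Count DREAM sick leave and register-based resource use from randomisation. Keep the window after surgery as a supporting analysis. State the end date as well, preferably one year after the surgery date planned before allocation, so that the length of the window does not depend on the arm.
4. Report by arm the number not operated and the interval from randomisation to surgery.
5. State whether QALYs before surgery are counted. This is possible only if EQ-5D was collected close to randomisation, which the article does not say.

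Cost: mostly wording. Register data can be drawn back to randomisation. A few extra questionnaires are needed for patients not operated, and since recruitment ended in July 2013 some may be late. Self-reported cost items before surgery may be incomplete, so that period may have to rely on registers. The sample size does not change.

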**Discussion:**

It is expected that the intervention can provide better functional outcome, less pain and earlier return to work after lumbar spinal fusion surgery. By combining knowledge and evidence from different knowledge areas, the project aims to provide new knowledge that can create greater consistency in patient treatment. We expect that the results can make a significant contribution to development of guidelines for good rehabilitation of patients undergoing lumbar spinal fusion.

**Trial registration:**

Current Controlled Trials ISRCTN42281022.

## Background

For sufferers of chronic and severe back pain, lumbar spinal fusion (LSF) surgery is a commonly offered treatment strategy when conservative treatment has failed [1,2]. In the past two decades reports have indicated significant increases in spinal fusion rates in the western countries, with the largest increase seen in the US. Here the annual age and sex adjusted rates of LSF procedures increased with 220% in the period 1990 – 2000 [3] and another 170% in the period 1998–2008 [4]. These rises are in part due to advances in surgical fusion techniques and devices, e.g. the approval of intervertebral fusion cages in 1996, intended to improve postoperative outcomes [5,6]. The increasing number of LSF operations and the consequent increased costs and risk of complications and adverse events [6-9] may be justified by the benefits of the procedure. But the efficacy of LSF for degenerative spinal disorders has not yet been established, as published reviews on the subject disagree [10-12]. One review including randomized, nonrandomized and retrospective studies concluded that the body of literature supports LSF as a viable treatment option for chronic LBP [11]. Two other reviews included only randomized controlled studies (RCT) comparing LSF to conservative treatment [10,12]. The earliest review concluded that robust conclusions on the efficacy of LSF could not be made. In the latter publication the authors stated that there is strong evidence that LSF is no more effective than conservative treatment. In both reviews the comparable effect of the conservative treatment was in evidence only with the use of structured rehabilitation with a cognitive-behavioural approach (CBT). Whether an additive effect can be achieved by combining LSF with a postoperative rehabilitation strategy applying CBT has been investigated in only one study [13]. Here, LSF followed by a 12 week intervention combining CBT and a structured exercise program resulted in significantly better outcomes on disability, pain and return to work compared to LSF plus standard rehabilitation. The standard rehabilitation consisted of a 12 week home based exercise program, commencing with one instruction from the physical therapist at the hospital at discharge. Another RCT including behavioural elements in the rehabilitation intervention following LSF similarly found benefits of the intervention, compared to both 8 weeks supervised exercise and to a video-guided home-based exercise program similar to that of Abbott et al. [14].

The idea of using CBT in combination with LSF seems rational, as psychosocial factors have become increasingly accepted as potentially important determinants of outcomes following spine surgery [15-18]. In particular, characteristics such as maladaptive coping strategies, fear-avoidance beliefs, preoperative anxiety and pain catastrophizing seem to be predictive of worse outcomes in pain, function and quality of life after surgery [15-18]. Modifying these traits, and thereby improving pain levels, disability and quality of life, seems to be achievable through the application of CBT [13,19-21].

An additional two parameters seem important in successful rehabilitation of surgically treated CLBP patients. The first is the management of the (CBT) rehabilitation by a multidisciplinary team, which two studies have found to be an important key factor in a population of severely disabled CLBP patients [22,23]. However, no studies including both CBT and multidisciplinary management in the rehabilitation strategy were found. The second parameter concerns the timing of rehabilitation. In the published studies on LSF patients, all but one initiate the rehabilitation intervention after surgery. It may be questioned, though, whether a better effect can be achieved by initiating an intervention already prior to surgery. One study by Nielsen et al. [24] investigated the effect of prehabilitation and early postoperative rehabilitation (presurgical training, analgesics and nutrition) compared to standard care. Patients in the intervention group reached the recovery milestones faster and left hospital earlier. A number of studies on preoperative interventions for populations of hip- and knee arthroplasty patients point to the same result, namely a benefit of initiating the intervention already prior to surgery [25,26]. None of these studies involve CBT or multidisciplinary strategies in their (p)rehabilitation.

On this basis we find it relevant to design a multidisciplinary rehabilitation strategy using a CBT approach, initiated prior to fusion surgery. The purpose of this paper is to describe the theoretical basis and the details of the intervention used in the study. This is in accordance with international recommendations for the development and evaluation of complex interventions in clinical trials [27].

### Defining cognitive-behavioural therapy

The biopsychosocial approach of CBT focuses on the complex interplay of cognitive, emotional, behavioural and social factors and how they interact with the biomedical factors. The main assumption is that a person’s thoughts and beliefs about their problem will influence their feelings and physiologic reactions and their consequent behaviours [28-30]. The role of behaviour is important, as people often act in ways that serve to maintain the unhelpful beliefs of the individual, and in this way a vicious circle persists. This strong link between beliefs predicting behaviour has been shown in several studies in CLBP patients [31,32]. Consequently, the goal of cognitive behavioural therapy is to identify and challenge maladaptive thoughts, and consequently modify feelings and behaviours, and thereby the experience of pain. The basic assumptions about pain behaviour and the relevant techniques applied for cognitive and behavioural therapy are as follows.

*The cognitive aspect* of CBT is based on Beck’s cognitive model promoting the idea, that a person’s cognition has an impact on their mood and emotions, their bodily reactions and their behaviour [28]. On a general level, three cognitive levels can be described. They are 1) (negative) automatic thoughts, being thoughts that surface quickly and automatically when a person is in a particular situation, e.g. “my boss will think less of me”, when being late for a meeting 2) Underlying assumptions, being unconscious and unspoken assumptions that govern our everyday behaviour. They can be positive, e.g. “if I achieve well in school, my parents will respect and love me” and correspondingly negative “If I fail this test I will make my parents unhappy and they will dislike me”. These assumptions cause us to live by rules, often expressed as what one “ought to” or “should” do to fulfill the underlying assumptions. 3) Schematas, being our fundamental perception of our selves, other people and the context in which we exist. A person usually possesses both positive (I’m respectable/lovable/trustworthy) and negative (I’m boring/unintelligent) schematas. The techniques used in cognitive therapy focus mainly on intervening on the first level, namely the thoughts, beliefs and expectations, that contribute to the negative emotions associated with chronic pain. Therefore the major goals of cognitive techniques are 1) help the patient become aware of how negative thoughts affect their mood, behaviour and pain and 2) challenge and modify the thoughts and through that promote improved pain coping. The techniques frequently applied are cognitive restructuring, problem solving, distraction and prevention of relapses.

Where the focus of the cognitive elements are on thoughts, beliefs and expectations, the main focus of *the behavioural aspect* is on a person's behaviours. The notion of behavioural therapy lends from the learning principles of operant conditioning, maintaining that social learning processes may account for instances where pain behaviours persist when healing could have occurred [33]. For instance, a worried parent may reinforce a pain behaviour of activity avoidance in his or her child. The two major goals of the behavioural therapy are hence 1) to increase the frequency of adaptive, well-suited behaviours and 2) to decrease maladaptive pain behaviours. Behavioural techniques used to achieve these goals are activity pacing, scheduling of pleasant activities, time-contingent medication and social reinforcement.

#### **
*Catastrophizing and fear-avoidance belief*
**

As can be summarized from the above description, a person’s negative beliefs, thoughts and expectations may cause them to behave and cope in a maladaptive manner in relation to their pain. Particularly fear-avoidance belief, catastrophic thinking and a feeling of helplessness and lack of control seem to be associated with passive coping strategies like rest and avoidance behaviour. The fear-avoidance model perceives catastrophic thinking as a prerequisite and an elementary factor for the development of avoidance behaviours [34]. It suggests how individuals with negative beliefs about pain will have a pain perception that is imbued with catastrophic interpretations. In an attempt to avoid this perceived catastrophic threat the person engages in avoidance behaviour, becoming gradually more deconditioned and disabled. As the patient engages in avoidance behaviour, he avoids an increasingly larger array of movements and activities and may spend a lot of time resting. The use of such passive (maladaptive) coping strategies may delay or in the worst case obstruct rehabilitation of the patient after the operation. The parts of the back affected by the operation (ligaments, muscles, nerves) will not gain the necessary strength and flexibility, if not exposed to a gradually larger strain according to recommendations. The tissue becomes weak and more prone to overloading, which again causes pain. Over time the patient may become increasingly more disabled and limited in work and social life with a consequent reduction in their quality of life. The fear-avoidance model, as presented by Vlayen and Linton [35] is depicted in Figure 1. As described earlier, interventions that have used CBT approaches to target catastrophizing and fear-avoidance behaviours have shown an association with a reduction in pain behaviours, physical disability and depression in both surgical and non-surgical CLBP patients [13,20,21,36,37].

